### **4 STUDY POPULATION**

#### **4.1. INCLUSION CRITERIA**

For inclusion in the COPD patients should fulfill the following criteria:

1. Provision of informed consent prior to any study specific procedures.
2. Female or male subjects aged 40-85 years inclusive at Visit 1.
3. Documented history COPD with a post-bronchodilator FEV1/FVC<0.70 and a post-bronchodilator FEV1<80% of predicted normal value at screening (spirometry will be used for this criteria assessment).
4. Current smoker or ex-smoker with a tobacco history of  $\geq 10$  pack-years (1 pack year = 20 cigarettes smoked per day for 1 year).
5. Women of childbearing potential (WOCBP) must use a highly effective form of birth control (confirmed by the Investigator).
  - Women <50 years old would be considered postmenopausal
6. At least a CAT value > 10 at Visit 1.

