## OUTLINE TRIALS APPLICATION

## 1. STUDY SYNOPSIS

|                                             |                                                                                                                                                                                                                                                                                                                                                                                                                                                                                                                                                                                       |
|---------------------------------------------|---------------------------------------------------------------------------------------------------------------------------------------------------------------------------------------------------------------------------------------------------------------------------------------------------------------------------------------------------------------------------------------------------------------------------------------------------------------------------------------------------------------------------------------------------------------------------------------|
| COORDINATING INVESTIGATOR            | [name]. med. [name], Medaimun GmbH & Allergologie, Pneumologie und Mukoviszidose, Goethe-Universität; [name]; [name] [contact]; [contact] E-mail: [contact]                                                                                                                                                                                                                                                                                                               |
| TITLE OF STUDY                       | A double-blind, placebo controlled, randomized crossover trial to characterize the mucolytic effectiveness of Tylaxopol, Tacholiquin ® in chronic bronchitis                                                                                                                                                                                                                                                                                                                                                                                                                          |

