| CONDITION                            | Mucolytic treatment in chronic bronchitis                                                                                                                                                                                                                                                                                                                                                                                                                                                                                                                                             |
| OBJECTIVE(S)                         | To evaluate the mucolytic activity of Tylaxopol compared to saline (0.9%) in chronic bronchitis patients. Lung function parameters, biomarker profiles in sputum and serum, and clinical symptoms by standardized questionnaires [COPD activity index (CAT), Baseline Dyspnea Index (BDI) & Transition Dyspnea Index (TDI)] will be evaluated in response to Tylaxopol vs. saline in chronic bronchitis patients.                                                                                                                                                                     |
| INTERVENTION (S)                     | Chronic bronchitis patients (will be randomly assigned to either inhaled Tacholiquin® 1% 5ml or saline solution each three times daily for 3 weeks. After one week of washout Tylaxopol treated patients will receive saline solution and vice versa for another 3 weeks.                                                                                                                                                                                                                                                                                                             |
| KEY INCLUSION AND EXCLUSION CRITERIA | Key inclusion criteria: Patients aged between 40 and 85 years suffering from chronic bronchitis (COPD). Key exclusion criteria: Patients with other underlying chronic diseases.                                                                                                                                                                                                                                                                                                                                                                                        |

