**LIST OF ABBREVIATIONS**

|                  |                                                      |
|------------------|------------------------------------------------------|
| AE               | Adverse Event                                        |
| ATS              | American Thoracic Society                            |
| BC               | Blood count                                          |
| CAT              | COPD Activity Index                                  |
| CBA              | Cytometric Bead Array                                |
| COPD             | Chronic Bronchitis                                   |
| CRFs             | Case Report Forms                                    |
| IL-6             | Interleukin 6                                        |
| FEV 1 | Forced Expiratory Volume in 1 second                 |
| FVC              | Forced Vital Capacity                                |
| GCP              | Good Clinical Practice                               |
| L                | Liter                                                |
| Mg               | Milligrams                                           |
| RBC              | Red Blood Cell                                       |
| RV               | Residual volume                                      |
| SABA             | Short-acting beta-2-agonists                         |
| SAE              | Serious Adverse Event                                |
| SD               | Standard deviation                                   |
| SUSAR            | Suspected, Unexpected, Serious Adverse drug Reaction |
| RV/TLC           | Functional residual capacity                         |
| WBC              | White Blood Cell                                     |

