## 1 BACKGROUND AND RATIONALE FOR THE STUDY

In the classical phenotype of chronic bronchitis, mucus hypersecretion is the key presenting symptom and its contribution to airflow obstruction and has been the subject of debate for a long time (1). By the 1950s it was known that tobacco smoking was associated with chronic cough and sputum production, and that smokers who developed chronic bronchitis had impaired lung defences, a condition favouring colonisation and infection of the lower airways (2). Biopsies showed that the excess mucus production which defined chronic bronchitis was associated with enlarged bronchial glands and that an approximate relationship existed between the presence of chronic bronchitis and emphysema (3). It is well established that chronic mucus hypersecretion is significantly and consistently associated with both an increase in forced expiratory volume in 1 s (FEV1) decline and an increase of subsequent hospitalisation (4-6).

A large number of studies have been performed on the use of mucolytic drugs in the treatment of chronic bronchitis and chronic obstructive bronchitis (COPD). The outcomes have been reviewed in several meta-analyses (7, 8). Overall, there was a significant reduction in exacerbations (0.05 per patient per month) and the number of days with disability (0.56 days per patient per month). Mucolytics were well tolerated and the number of adverse events was lower than with placebo (7).

The aim of the present study is to assess the effects of the “old” mucolytic agent, Tacholiquin ® compared to saline (0.9%) in patients with chronic bronchitis (COPD). Tacholiquin ® -Tyloxapol is a polymeric covalent compound with multiple mucolytic actions. Tyloxapol is a product which has been developed in Europe in the fifties; therefore the standards used for its development are partially different to those currently applied. Despite extensive clinical evidence of its clinical usefulness little is known about the mucolytic activity of Tyloxapol compared to saline solution.

- There are no randomized double-blind, placebo controlled trials available demonstrating possible superiority of Tyloxapol vs. saline.
- No data exists of mucolytic action on quality of life and lung function parameters in chronic bronchitis
- No specific studies are available in human investigating biomarker profiles (in sputum and serum after Tyloxapol inhalation)

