#### **4.2. EXCLUSION CRITERIA**

1. Clinically important pulmonary disease other than COPD (e.g. active lung infection, clinically significant bronchiectasis, pulmonary fibrosis, cystic fibrosis, hypoventilation syndrome associated with obesity, lung cancer, alpha 1 anti-trypsin. deficiency and

---

primary ciliary dyskinesia) or another diagnosed pulmonary or systemic disease that is associated with elevated peripheral eosinophil counts (e.g. allergic bronchopulmonary aspergillosis/mycosis, Churg-Strauss syndrome, hypereosinophilic syndrome).

2. Female Any disorder, including, but not limited to, cardiovascular, gastrointestinal, hepatic, renal, neurological, musculoskeletal, infectious, endocrine, metabolic, haematological, psychiatric, or major physical impairment that is not stable in the opinion of the Investigator and could:

- Affect the safety of the subject throughout the study
- Influence the findings of the study or their interpretation
- Impede the subject's ability to complete the entire duration of study

3. Documented Unstable ischemic heart disease, arrhythmia, cardiomyopathy, heart failure, renal failure, uncontrolled hypertension as defined by the Investigator, or any other relevant cardiovascular disorder as judged by the Investigator that in Investigator's judgment may put the patient at risk or negatively affect the outcome of the study.

4. Treatment with systemic corticosteroids and/or antibiotics, and/or hospitalization for a COPD exacerbation within 4 weeks prior to (Visit 1)

5. Acute upper or lower respiratory infection requiring antibiotics or antiviral medication within 4 weeks prior to (Visit 1)

6. Pneumonia within 4 weeks prior to (Visit 1), based on the last day of antibiotic treatment or hospitalization date, whatever occurred later. The subject cannot be re-screened if this exclusion criterion is met.

7. History of anaphylaxis to Tacholiquin ®.

8. Long term oxygen therapy (LTOT) with signs and/or symptoms of cor pulmonale, right ventricular failure or evidence by echocardiogram or pulmonary artery catheterization of moderate to severe pulmonary hypertension. In order to be admitted to the trial subjects on LTOT have to be ambulatory and be able to attend clinic visits.

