### **9.3. SAMPLE SIZE CALCULATION**

The sample size is difficult to calculate. In a previous thesis of our group sputum weight was found to be of little variation at two separate time points in patients with asthma. After inhalation of hypertonic saline induced sputum of 20 asthmatics was  $4.9 \pm 2.41$  g and  $4.78 \pm 1.6$  g respectively.

These data are in keeping with a previous publication in chronic bronchitis with bronchiectasis. The authors found after inhalation of hypertonic a sputum weight of 5.3 g compared to 3.17 g after saline inhalation (24).

Therefore the calculated sample size of the present study is based on an expected difference for Tacholiquin ® in sputum weight of about 1.2 g corresponding to about 40% of that expected for saline with a standard deviation of  $s=1.7$  g roughly

corresponding to a correlation between sputum weights of  $\rho=0.75$ . Then a sample size of 20 achieves a power of 80%.

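### The inclusion and exclusion lists (4.1, 4.2) do not put the chronic bronchitis of the title and synopsis into operation, so patients without chronic sputum production can enter a trial with a sputum-weight endpoint

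*Protocol*

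**What the plan says.** **Target condition.** The title sets out "to characterize the mucolytic effectiveness of Tylaxopol, Tacholiquin ® in chronic bronchitis". The synopsis gives as key inclusion "Patients aged between 40 and 85 years suffering from chronic bronchitis (COPD", with COPD in brackets as an equivalent term, and the list of abbreviations expands COPD as "Chronic Bronchitis". The background (section 1) states: "In the classical phenotype of chronic bronchitis, mucus hypersecretion is the key presenting symptom". It also describes excess mucus as the defining feature of the condition.

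**Primary endpoint.** Sections 2.2, 7.1.1 and 9.4 use sputum weight after three weeks of tyloxapol compared with that after three weeks of saline, within patient.

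**Operative criteria.** Section 4.1 has six items: consent, age 40 to 85, airflow limitation ("Documented history COPD with a post-bronchodilator FEV1/FVC<0.70 and a post-bronchodilator FEV1<80% of predicted normal value at screening"), at least 10 pack-years, contraception, and "At least a CAT value > 10 at Visit 1". Section 4.2 removes, among others, patients with "clinically significant bronchiectasis", but not patients who bring up no sputum. The definition of an evaluable patient in section 3 does not mention sputum either.

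**How the sample is obtained.** Section 7.3.1 calls it induced sputum, collected after salbutamol and then the nebulised study medication. In the control period that medication is 0.9% saline (5.1, 5.2).

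**Planning weights.** Section 9.3 cites 20 asthmatics with 4.9 g and 4.78 g after hypertonic saline, and then says "These data are in keeping with a previous publication in chronic bronchitis with bronchiectasis". In that publication the weights were 5.3 g after the hypertonic solution and 3.17 g after saline.

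**The concern.** The feature that characterises the target disease is also what the primary endpoint measures, and 4.1 and 4.2 never test for it. A breathless patient with COPD, a smoking history and a CAT total above 10 qualifies without any chronic cough or sputum. The CAT criterion does not help, because it uses the total and sets no condition on cough or sputum.

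Two things are at stake. A patient with little mucus to mobilise may show a smaller treatment difference than planned, which pulls the mean difference towards zero and costs power. And the patients studied would be COPD patients selected by airflow, which is not clearly the population in the title. With about 20 patients at one centre, a few such entries would make a null result hard to read: it could mean no mucolytic effect, or little mucus to act on.

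**Working it through.** **1. The criteria against the target.**

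| Place | What it requires about sputum or chronic bronchitis |
|---|---|
| Title, objective | Chronic bronchitis is the condition studied |
| Synopsis, key inclusion | Names chronic bronchitis, equated with COPD, without a definition |
| 4.1, six inclusion items | Nothing |
| 4.2, ten exclusion items | Nothing that removes a patient without sputum |
| Section 3, evaluable patient | Nothing |
| 6.2.1, Visit 1 | Randomisation is listed before the first inhalation and sputum collection |

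The last row shows that the first sample comes after randomisation. In the present visit order, giving a sample does not act as an entry condition.

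**2. The planning weights against the enrolled population.** The asthma weights (4.9 g and 4.78 g) were obtained after hypertonic saline. The only weight after saline, 3.17 g, comes from chronic bronchitis with bronchiectasis. The planned 1.2 g is described as about 40% of the saline value, which implies 1.2 / 0.40 = 3.0 g. Against 3.17 g it is 1.2 / 3.17 = 38%. Clinically significant bronchiectasis is excluded by 4.2, and none of the cited weights comes from COPD patients selected by airflow and smoking.

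**3. The protocol's own sample size.** Inputs from 9.3 and 9.5: difference 1.2 g, SD 1.7 g, correlation 0.75, two-sided alpha 0.05, n = 20, stated power 80%. Read as the SD of the within-patient difference, 1.7 g implies a per-treatment SD of 1.7 / sqrt(2 × (1 − 0.75)) = 2.40 g, close to the 2.41 g quoted for the asthmatics. Paired t-test power comes from the noncentral t with n − 1 degrees of freedom and noncentrality (1.2 / 1.7) × sqrt(n):

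- n = 18 gives 80.6%. This is the smallest n that reaches 80%, and it is the synopsis per-protocol number.
- n = 20 gives 84.9%.

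The stated 20 patients for 80% power is therefore reproduced, slightly on the safe side. This point does not dispute it.

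**4. Illustration of dilution.** Let f be the share of analysed patients with a mean difference of zero. **The documents give no value of f, so the shares below are assumptions.**

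- Mean difference: 1.2 × (1 − f).
- Variance, case A (these patients show exactly zero): (1 − f) × 1.7² + f(1 − f) × 1.2².
- Variance, case B (their differences keep the 1.7 g SD): 1.7² + f(1 − f) × 1.2².

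| f | Mean (g) | SD A (g) | Power A, n=20 | SD B (g) | Power B, n=20 |
|---|---|---|---|---|---|
| 0 | 1.20 | 1.70 | 85% | 1.70 | 85% |
| 10% | 1.08 | 1.65 | 79% | 1.74 | 75% |
| 25% | 0.90 | 1.56 | 69% | 1.78 | 58% |
| 50% | 0.60 | 1.34 | 48% | 1.80 | 29% |

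At the per-protocol n = 18, case A gives 81%, 74%, 64% and 43% for the same four shares.

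**5. Partial response.** If these patients instead show half the effect (0.6 g) and keep the 1.7 g SD, the mean is 1.2 × (1 − f) + 0.6 × f and the variance is 1.7² + f(1 − f) × 0.6². Power at n = 20 is then 81%, 74% and 60% for f = 10%, 25% and 50%.

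**The case against.** The strongest reply has three parts.

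**The synopsis does name chronic bronchitis.** A reader might infer that the protocol nowhere requires the condition. That is too strong, because the synopsis key inclusion states it. What stands is narrower. The term is undefined and interchangeable with COPD there and in the abbreviation list, and the full list in 4.1 does not carry it over, so it adds nothing an investigator can check.

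**The sputum is induced.** A reader might infer that every patient without chronic sputum contributes a difference near zero, or that the planning figures presuppose chronic producers. The documents establish neither. Section 7.3.1 describes collection after nebulisation, and the asthmatics in 9.3, who are not described as chronic producers, gave nearly 5 g. But that yield followed hypertonic saline. It does not show what 0.9% saline or tyloxapol would bring up in such patients.

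**The direction of the error is benign.** In a blinded, randomised, within-patient comparison these patients dilute the effect and favour neither treatment. At a 10% share with zero differences, power is 79%, practically the stated 80%. This stands, and it limits the severity. It does not remove the mismatch between the titled population and the one the criteria admit, and an analysis plan cannot restore a population that was not enrolled.

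**Conclusion.** The point holds as a gap between the stated target and the operative criteria. Sections 4.1 and 4.2 admit COPD patients without chronic sputum production to a chronic bronchitis trial whose primary endpoint is sputum weight.

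Its size is not known. Power at n = 20 falls from 85% to between 79% and 48% for zero-difference shares of 10% to 50%, or to between 75% and 29% if those patients' differences keep the 1.7 g SD. Partial response softens this. All of these figures rest on assumed shares and on 1.7 g being the SD of the within-patient difference.

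A reader might go on to conclude that the trial could say nothing about chronic bronchitis, or that it could not proceed unchanged. The documents do not support that: they give no share of non-producers, and the sampling procedure may yield sputum from some of them. The right grade is should-fix, as a cheap improvement.

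**What to change.** - **Section 4.1:** add an inclusion criterion, answered from history at Visit 1, of chronic cough with current sputum production. The sponsor should choose and state the definition. The COPD, smoking and CAT criteria can stay.
- **Synopsis:** align the key inclusion line with the new criterion, and stop using COPD and chronic bronchitis as synonyms there and in the abbreviation list.
- **Section 9.3:** state that the planning weights come from asthmatics after hypertonic saline and from chronic bronchitis with bronchiectasis, and that clinically significant bronchiectasis is excluded from this trial.

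**Cost.** No new procedure is needed, because medical history is already taken at Visit 1. Screening will lose more patients. The synopsis plans 26 assessed for 20 allocated, which leaves room for 6 failures of any kind. If 10%, 25% or 50% of candidates failed the new criterion, 20 allocations would need about 20 / 0.90 = 23, 20 / 0.75 = 27 or 20 / 0.50 = 40 assessed, before any other failure. The number to be screened and the recruitment period should be revisited with the amendment.

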| Inclusion/ Exclusion                          | X                                  |                   |                   |                            |                   |                    |
| Physical Examination Vital Signs              | X                                  | X                 | X                 | X                          | X                 | X                  |
| Lung function (Bodyplethys.)                  | X                                  | X                 | X                 | X                          | X                 | X                  |
| Post Reversibility Lung function              | X                                  | X                 | X                 | X                          | X                 | X                  |
| Urine Pregnancy testing           | X                                  | X                 | X                 | X                          | X                 | X                  |
| Laboratory examinations           | X                                  |                   |                   |                            |                   |                    |
| COPD Assessment Test (CAT) handover           | X                                  | X                 | X                 | X                          | X                 | X                  |
| Collection and Review of BDI / TDI St George  | X                                  |                   | X                 |                            | X                 | X                  |

---

|                                            |   |   |   |   |   |   |
|--------------------------------------------|---|---|---|---|---|---|
| Inhalation of medication                   | X | X | X | X | X | X |
| Lung function after Sputum collection      | X | X | X | X | X | X |
| Monitoring Ease of expectoration           | X | x | x | x | x | x |
| Nebulizer and Drug dispensation            | X |   |   | X |   |   |
| Collection of trial drug/ Compliance check | x | x | X | x | x | X |
| Recording of Adverse Events                |   | X | X | X | X | X |
| Appointment for the next visit             | X | X | X | X | X |   |

1) If applicabel

2) Laboratory examinations : Hematology Makrophagen Activation test

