9. Any clinically significant abnormal findings in physical examination, vital signs, haematology, or urinalysis during Visit 1, which, in the opinion of the Investigator, may put the subject at risk because of his/her participation in the study, or may influence the results of the study, or the subject's ability to complete entire duration of the study.

10. Use of immunosuppressive medication, including rectal corticosteroids, high potency topical corticosteroids and systemic steroids within 28 days prior to (Visit 1).

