#### 6.1.1. RECRUITMENT PROCEDURE

At Visit 1 before any assessment necessary for the study, the COPD patient will be informed by the physician according to the “Patient information” sheet. The patient will then give a written consent by signing the Patient Consent. As soon as the specific inclusion and exclusion criteria at Visit 1 have been checked, eligible patients will be assigned a randomization number in ascending order. They will then start double-blind trial treatment.

Additional visits can be scheduled and performed according to the investigators judgment of how to best manage the patient. At these visits in addition to recording any SAEs, AEs and concomitant medication use, a physical examination, vital sign assessment and lung function tests are to be performed.

Any unscheduled visits are to be recorded in the other clinical visits CRFs.

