### 6.2. **PROCEDURE BY VISIT**

#### 6.2.1. **METHODS AND MEASUREMENTS**

##### **Visit procedures at screening visit and before treatment phase A (Visit 1)**

- Patient information/Informed consent
- Date of visit
- Demographic data,
- Medical history and concomitant diseases
- Physical examination / Vital signs
- Concomitant medications
- Bodyplethysmography
- Bronchodilator response to Salbutamol
- Completing Questionnaires (CAT, BDI, St George)
- Inclusion/exclusion criteria

- Randomisation and drug dispensation
- Laboratory examination (including Urinalysis)
- Inhalation of blinded medication by nebuliser
- Sputum collection
- Recording side effects
- Recording “ease of expectoration”.
- Lung function monitoring up to one hour after sputum collection
- Lung clearance index one hour after inhalation
- Dairy explanation
- Appointment for the next visit

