## URINE PREGNANCY TESTS

Pregnancy tests are obtained from all female volunteers of child-bearing potential. At Visit 1, a urine pregnancy test is obtained.

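### Inclusion criterion 5 as worded treats women under 50 as postmenopausal, so women aged 40–49 escape the contraception rule, and no entry criterion excludes pregnancy

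*Protocol*

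**What the plan says.** Section 4.1 admits "Female or male subjects aged 40-85 years inclusive at Visit 1". Criterion 5 of that section asks women of childbearing potential to use highly effective contraception, confirmed by the investigator. It has one sub-bullet: "Women <50 years old would be considered postmenopausal". The protocol does not otherwise define childbearing potential or postmenopausal status.

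On testing, the section on urine pregnancy tests says "Pregnancy tests are obtained from all female volunteers of child-bearing potential" and then "At Visit 1, a urine pregnancy test is obtained". The flow chart marks the test at all six visits, with the footnote "If applicabel".

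On entry, section 4.2 lists ten exclusion criteria. The nearest to this point is criterion 9, which covers "Any clinically significant abnormal findings in physical examination, vital signs, haematology, or urinalysis during Visit 1" where the investigator judges that the finding matters. Section 4.3 lists pregnancy as a reason for withdrawal. Section 6.1.1 sets the order at Visit 1: "As soon as the specific inclusion and exclusion criteria at Visit 1 have been checked, eligible patients will be assigned a randomization number", after which blinded treatment starts.

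**The concern.** A menopause definition under a contraception criterion normally serves to release women who can no longer conceive. Here it releases the wrong group: being younger than 50 is by itself enough to count as postmenopausal. A site that followed the text would ask no contraception of women aged 40–49 and could decide that the pregnancy test does not apply to them.

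The second part is independent of the first. Even for a woman who is tested, no written rule makes a positive result at Visit 1 a bar to randomisation and first dosing. The protocol treats pregnancy as incompatible with staying in the trial but does not make it a reason not to enter. What is at stake is patient safety and clear eligibility, not the efficacy analysis.

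**Working it through.** No arithmetic applies beyond counting, so the check follows the text through.

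**1. Who is covered.** Both sexes are eligible from 40 to 85 years (section 4.1, criterion 2). The sub-bullet applies below 50. The women affected are therefore those aged 40–49.

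**2. What follows for contraception.** Under 50 → postmenopausal (sub-bullet) → not of childbearing potential → no contraception duty under criterion 5. The middle step is an inference, because childbearing potential is not defined, but the sub-bullet has no other evident function where it stands. For women of 50 and over, the main sentence of criterion 5 still applies to any who are of childbearing potential, but no age-specific menopause rule is given.

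**3. What follows for testing.** The pregnancy-test section limits the test to women of childbearing potential, and the flow-chart footnote limits it to where it applies. On the reading in step 2, a woman aged 40–49 falls outside both.

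**4. Whether any entry criterion names pregnancy or lactation.**

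| Place | Count | Naming pregnancy or lactation |
|---|---|---|
| Inclusion criteria (4.1) | 6 | 0 |
| Exclusion criteria (4.2) | 10 | 0 |
| Withdrawal criteria (4.3) | 8 | 1 (pregnancy) |

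Exclusion 9 refers to urinalysis. The protocol describes the urine dipstick under laboratory examinations and the pregnancy test under its own heading, so urinalysis does not clearly include the pregnancy test. Exclusion 2 opens with a stray word, Female, and then describes unstable disorders; it says nothing on pregnancy.

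**5. Whether a test result must be known before dosing.** Section 6.1.1 ties randomisation to the criteria check at Visit 1. The Visit 1 procedure list in section 6.2.1 contains no pregnancy test, and it places randomisation and dispensing above "Laboratory examination (including Urinalysis"). The list is not stated to be chronological, so this shows only that nothing requires the result first.

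**6. Consistency of the testing schedule.**

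| Place | Visits with a pregnancy test |
|---|---|
| Flow chart | 6 of 6 |
| Pregnancy-test section | Visit 1 named |
| Visit procedure lists (6.2.1) | 0 of 6 |

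**The case against.** The best reply is that no clinician would apply the sub-bullet literally. It makes women postmenopausal because they are younger, its phrasing reads like a sentence that has lost its conditional clause, and the stray word in exclusion 2 shows that text was damaged nearby. The investigator must confirm contraception, a urine test is named at Visit 1 and marked at every visit in the flow chart, and pregnancy is a withdrawal reason. Exclusion 9 also gives the investigator discretion. Knowingly randomising a pregnant woman is therefore unlikely in practice.

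Much of this is fair. The exemption is inferred, many investigators would notice the slip, and the number of women involved may be zero. Whether the missing words were lost in the source or in the reading of the PDF cannot be settled from the text, although nothing marks a redaction. The differences in the testing schedule are a lesser editorial point: the pregnancy-test section does not say that Visit 1 is the only test, and the visit lists omit other items that the flow chart contains, such as the compliance check. The case for excluding lactation rests on general practice, not on anything in this protocol.

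The safeguards do not remove the defect, however. Confirmation of contraception and testing apply only to women classed as being of childbearing potential, which is the class that the sub-bullet distorts. Exclusion 9 is discretionary and does not name a pregnancy test. The intended condition cannot be recovered from the protocol, so each investigator would have to supply one. The background and tolerance sections describe long use without marked harm but do not address pregnancy.

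**Conclusion.** The concern holds: the sub-bullet is wrong as written, and pregnancy is missing from the entry criteria. The finding rests on the literal text and on one inference, that a woman called postmenopausal under criterion 5 is released from its contraception duty.

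The size in patients cannot be stated. Section 3 plans 24 patients and the protocol gives no expected split by sex or age, so the number of women aged 40–49 may be none or a few. There is no effect on the primary endpoint, the sample size or the analysis. It should be corrected because it is a safety rule that gives the wrong answer when followed. Confidence is high in the wording defect; how far it would have led to harm is unknown.

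**What to change.** - Reword the sub-bullet so that a woman under 50 counts as postmenopausal only if a stated clinical condition is met, for example a defined period of amenorrhoea, with hormonal confirmation if the sponsor wishes. Otherwise she is treated as being of childbearing potential.
- State the corresponding rule for women aged 50 and over.
- Add pregnancy to section 4.2 as an exclusion, defined by a positive urine test at Visit 1 that is read before randomisation. Add lactation alongside it.
- Give the same testing schedule in the flow chart, the pregnancy-test section and the visit lists.

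The cost is amended wording. The flow chart already marks the urine tests, so no new procedure is needed.
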